## Abstract

**Background:**

Obesity remains a major public health challenge, demanding cost-effective and scalable weight management programs. Delivering key treatment components via mobile technology offers a potential way to reduce expensive in-person contact, thereby lowering the cost and burden of intensive weight loss programs. The ENGAGED study is a theory-guided, randomized controlled trial designed to examine the feasibility and efficacy of an abbreviated smartphone-supported weight loss program.

**Methods/design:**

Ninety-six obese adults (BMI 30–39.9 kg/m^2^) will be randomized to one of three treatment conditions: (1) standard behavioral weight loss (STND), (2) technology-supported behavioral weight loss (TECH); or (3) self-guided behavioral weight loss (SELF). All groups will aim to achieve a 7% weight loss goal by reducing calorie and fat intake and progressively increasing moderate intensity physical activity to 175 minutes/week. STND and TECH will attend 8 group sessions and receive regular coaching calls during the first 6 months of the intervention; SELF will receive the Group Lifestyle Balance Program DVD’s and will not receive coaching calls. During months 1–6, TECH will use a specially designed smartphone application to monitor dietary intake, body weight, and objectively measured physical activity (obtained from a Blue-tooth enabled accelerometer). STND and SELF will self-monitor on paper diaries. Linear mixed modeling will be used to examine group differences on weight loss at months 3, 6, and 12. Self-monitoring adherence and diet and activity goal attainment will be tested as mediators.

**Discussion:**

ENGAGED is an innovative weight loss intervention that integrates theory with emerging mobile technologies. We hypothesize that TECH, as compared to STND and SELF, will result in greater weight loss by virtue of improved behavioral adherence and goal achievement.

**Trial registration:**

NCT01051713

## Background

Obesity remains a pressing public health problem. Approximately 36% of adults in the United States are obese (Body Mass Index (BMI) ≥ 30 kg/m^2^)
[1]. Globally, the World Health Organization estimates that approximately 500 million adults were obese in 2008
[2]. Obesity heightens the risk of a number of diseases, including type 2 diabetes, cardiovascular disease, obstructive sleep apnea, gallbladder disease, osteoarthritis, and several forms of cancer
[3-6]. Consequently, obesity creates significant economic burden: U.S. medical costs associated with obesity were $147 billion in 2008
[7].

The Diabetes Prevention Program (DPP) intensive lifestyle intervention, which targets decreasing caloric and fat intake and increasing moderate-to-vigorous intensity physical activity, has been successful in producing clinically significant weight loss and reducing the incidence of diabetes in pre-diabetic adults
[8]. In spite of its efficacy for weight loss and improving cardiometabolic outcomes, the DPP lifestyle intervention has not been widely adopted in its original form, primarily because it includes sixteen face-to-face sessions and sixteen to twenty-four optional maintenance meetings. This amount and type of contact is considered too burdensome and expensive to be a sustainable program
[9]. In an attempt to increase the reach of this program, the DPP protocol has been translated for implementation in real-world settings
[10] such as in a community YMCA
[11] and a community-based diabetes education program led by community health workers
[12]. Significant weight losses were produced ranging from 6.0-7.3% in both studies. However these programs may still have limited reach due to the 16–24 weekly group sessions required during months 1–6 and additional maintenance meetings during months 7–12
[11,12]. To date, studies that have reduced treatment intensity by reducing the number of in-person sessions have resulted in poorer weight loss outcomes
[13]. Therefore, the still unmet challenge of DPP implementation is how to reduce in-person contact without eliminating features considered essential for successful weight loss: social support, accountability, and feedback.

### Technology and weight loss interventions

Technology-based interventions hold great promise as a mechanism for disseminating efficacious weight loss programs to a broader portion of the population via a cost-effective, scalable platform
[14]. Many different technologies have been used in weight loss interventions including PDAs
[15,16], cell phone text messages
[17,18] and wearable physical activity monitors
[19,20]. However, Internet-based interventions have received the most empirical attention to date
[21]. Internet-based weight loss treatment findings have been mixed, and those programs that have achieved the highest weight losses have also included interactive tools, tailored feedback to participants, and in-person contact
[21-24]. Programs that are solely internet-based however, do not allow for the same level of interactivity, social support, and feedback that occurs during in-person interventions.

New generation handheld technologies have the potential to overcome many of the limitations of internet-based health behavior change interventions
[25]. Mobile phones are becoming ubiquitous: 46% of Americans own a smartphone, with rates even higher among minority groups
[26]. Smartphones provide an unprecedented opportunity for frequent and interactive feedback, tailored email or text reminders, and immediate access to social support from peers and coaches. Interactive smartphone applications can be used as a decision support tool to provide timely information on health behavior decisions occurring in real-time. These technological advances afford a promising opportunity to preserve the key components of intensive in-person treatment approaches (i.e., regular social support, accountability, and frequent feedback) while requiring fewer in-person sessions, thus, lowering the cost and broadening the accessibility of treatment. To test the feasibility and efficacy of this mobile technology-supported strategy, we have developed the E-Networks Guiding Adherence to Goals in Exercise and Diet (ENGAGED) study, a randomized controlled trial (RCT) that uses a theory-guided, technology-supported weight loss program.

### Theoretical framework

The conceptual basis for the ENGAGED study is Carver and Scheier’s control systems theory (CST) of self-regulation
[27]. CST posits that self-regulation can be understood in terms of feedback loops, wherein people: (1) set a goal, (2) self-monitor their current status to identify discrepancy from a goal, and then (3) modify their behavior to reduce perceived discrepancy. From a CST perspective, DPP’s efficacy can be attributed to helping participants (1) set appropriate caloric intake and physical activity goals, (2) self-monitor weight, eating behavior, and activity, and (3) adjust behaviors to reach the targets. According to CST, the core challenge in weight loss is aligning diet and activity with goals. Most weight loss efforts lose because traditional paper and pencil self-monitoring of diet and activity fails to provide salient, timely decision support and accurate feedback.

Using CST as a guiding framework, ENGAGED will develop a persuasive, interactive smartphone application designed improve the saliency, timeliness, and accuracy with which participants receive feedback on their daily dietary and activity goals. Participants will monitor dietary intake and wear a Bluetooth-enabled accelerometer to receive real-time feedback on objectively measured physical activity. Persuasively designed goal thermometers on the application will display current behavior and goals to highlight behavior-goal discrepancies. We posit based on CST that the experience of receiving consistent and immediate feedback from the ENGAGED technology should reinforce adherence to self-monitoring and healthy behavior change, both during and after in-person treatment ends.

### Social networks, peer support, and weight loss

Research on social networks and weight has elicited promising results. Christakis and Fowler
[28] reported that obesity can spread virally through social networks. Relatedly, other findings suggest that including friends and family as co-participants in weight loss treatment improves outcomes
[29]. However, not all overweight and obese adults have family or friends willing to join and/or support them in their weight loss efforts. Thus, additional strategies to provide peer support need to be identified. Social networking tools have gained popularity on many online commercial weight management programs, and preliminary evidence indicates that technology-supported social networking can be beneficial. Krukowski et al.
[30] found that use of social networking features in an online weight management program was positively associated with weight loss maintenance.

The ENGAGED study will utilize technology that enhances social networking capabilities on a smartphone application to promote the development and maintenance of a positive social network. The application will allow teammates who have been incentivized to help each other via a group weight loss competition to view each others’ adherence to daily self-monitoring goals. Additionally, the application allows team members to communicate with each other via private message board or peer-to-peer messaging. By capitalizing on team-based performance incentives and enabling team building through the ENGAGED social networking technology, we aim to extend support, encouragement, and accountability for behavioral change, between and after in-person group sessions.

### Study aims

Guided by CST and social networks research, the ENGAGED study will evaluate the feasibility and efficacy of a technology-supported weight loss program for obese adults. Specifically, the primary aim of the ENGAGED study is to conduct a three-group randomized controlled trial testing the efficacy of the ENGAGED technology-supported behavioral weight loss program, as compared to the same program delivered using standard paper and pencil self-monitoring, and self-guided behavioral weight loss supported by participants receiving DVD’s depicting DPP treatment. Primary outcomes include: (1) weight loss and (2) behavioral adherence, which is operationalized by (a) self-monitoring of diet and activity and (b) attainment of diet and activity goals. As a secondary outcome, the time spent administering the intervention by lifestyle coaches will also be examined to assess intervention costs. The second aim of the ENGAGED study is to test whether the weight loss in the technology-supported condition is mediated by behavioral adherence to self-monitoring and achievement of diet and activity goals.

We hypothesize that using a theory-guided, technology-supported weight loss treatment will result in clinically significant weight loss with fewer in-person sessions by preserving regular social support, accountability, and feedback via mobile technology. Further, we hypothesize that technology-supported weight loss treatment will result in greater weight loss compared to the traditional paper self-monitoring approach.

## Methods

### Study design

The research design is a 3 × 4 factorial with one between subjects factor (treatment condition) with three levels and one within subjects factor (time) with four levels (baseline, 3-, 6-, and 12-months). Participants will be randomized to one of three groups: a) Standard behavioral weight loss program (STND); b) technology-supported behavioral weight loss program (TECH); or c) self-guided behavioral weight loss program (SELF).

### Eligibility

A total of 96 participants who meet the inclusion and exclusion criteria listed in Table
1 will be recruited in two cohorts. Participants will be between 18–60 years old with a body mass index (BMI) between 30–40 kg/m^2^, weight stable for the past 6 months, not currently enrolled in a formal weight loss program or taking weight loss medications, and be willing to self-monitor and wear an accelerometer daily for 6 months. Participants will be excluded if they have any unstable medical conditions, are currently pregnant, or taking any medications known to influence weight. See Table
1 for a complete list of exclusion criteria.

**Table 1 T1:** ENGAGED inclusion and exclusion criteria

**Inclusion**	**criteria**
	• BMI 30.0-39.9 kg/m^2^
	• 18-60 years old
	• Interested in losing weight through diet and physical activity changes
	• Weight stable over the past 6 months
	• Not receiving concurrent weight loss treatment
	• Willing to self-monitor (on smartphone or paper) and wear an accelerometer daily for 6 months
	• Able to attend all assessments and group sessions
	• Have or be willing to learn basic technology usage skills
**Exclusion**	**criteria**
	• Has one or more of the following unstable medical conditions: uncontrolled hypertension or diabetes, angina pectoris, myocardial infarction, plantar fasciitis, transient ischemic attack, cancer undergoing active treatment, or cerebrovascular accident within the past 6 months
	• Has insulin-dependent diabetes, Crohn’s Disease, obstructive sleep apnea requiring use of a CPAP, plantar fasciitis
	• Requires use of an assistive device for mobility
	• Has been hospitalized for a psychiatric disorder in the past 5 years
	• Contraindications for moderate intensity physical activity
	• Currently taking any weight-loss medications or committed to following an incompatible dietary regimen
	• Currently pregnant, trying to get pregnant, or lactating
	• Current bulimia nervosa or binge eating disorder
	• Current substance or alcohol or dependence
	• Current attention deficit hyperactivity disorder or major depressive disorder
	• Currently taking medication(s) known to cause weight gain (i.e. Prednisone, Depakote, Diebeta, Diabinese, Cardura, Inderal, Zyprexa)
	• Expresses active suicidal ideation

### Recruitment and screening process

All study procedures are approved by the Institutional Review Board at Northwestern University. Participants will be recruited via flyers and advertisements in local newspapers and on public transportation. Interested candidates will be directed to a study website which includes study-related information and an online screening questionnaire to assess initial eligibility. Figure
1 illustrates the screening process.

**Figure 1 F1:**
[figure not shown]
ENGAGED Study Screening Flowchart.

#### Online screening

Participants will complete an initial online consent process prior to completing the online screener, which assesses height and weight, physical activity readiness, group session availability, and exclusionary weight loss practices (i.e. participation in a weight loss program or use of weight loss medications). Study staff will contact eligible participants within 1–4 days of completing an online screener to conduct a telephone screen.

#### Telephone screening

The telephone screen will review details of the study and review additional eligibility criteria including health status and medication use. Eligible and interested participants will be invited to attend a study orientation session and will be instructed to begin a one-week run-in period of dietary self-monitoring. If participants indicate a health condition such as type II diabetes or hypertension, medical clearance from a physician will be required prior to the pretreatment session in order to continue participation.

#### In-person orientation session

During the orientation session, complete details of the study will be given and an equipoise induction will be performed to ensure that participants are aware of the pros and cons of the treatment conditions and to minimize the risk of differential attrition
[31]. Participant questions will be answered and informed consent will be obtained from interested participants. Consented participants will complete the final in-person screening and baseline assessment, which includes assessing blood pressure and anthropometric measurements. In addition, participants will complete a smartphone competency task to evaluate their ability to use basic functions of a smartphone after instruction and will complete a brief interview to assess: binge eating disorder, bulimia nervosa, substance abuse and dependence, attention deficit hyperactivity disorder, and major depressive disorder. Eligible participants will also complete baseline questionnaires and wear an accelerometer for 10 days to measure current activity levels.

#### Pre-treatment session

At the pretreatment session, participants will return the accelerometer, meet with a dietician to complete a dietary recall, and engage in a brief treadmill activity. During the treadmill activity, participants will walk on a treadmill at a moderate intensity while reviewing ratings of perceived exertion to become familiar with the physiological signs of physical activities at this intensity.

### Randomization

Eligible participants will be scheduled for a group time and assigned to a team with seven other participants, all of whom will be randomized to the same condition. Group randomization will be completed by a statistician, and neither participants, nor coaches, will find out group assignment until the first group session. The intervention timeline is presented in Figure
2.

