### Team weight loss competition

In order to encourage members of each weight loss team to support each other’s behavioral adherence and weight loss, a team weight loss competition will be held at 3- and 6-months during each cohort. The team with the greatest weight loss percentage at each time point will win $400, to be divided evenly among the group members ($50 per team member).

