### Data analytic plan

#### Linear mixed modeling

Data will be analyzed on an intent-to-treat basis. The basic modeling approach will entail linear mixed models for longitudinal data. The primary aim is to test for treatment group differences on weight loss at 3-, 6-, and 12-months as well as differences in behavioral adherence and goal attainment at 3- and 6-months. Linear mixed models do not require that participants are measured at all time points, and therefore can include participants with missing data across time. In these analyses, we will examine changes across time by treating time as a nominal variable in the analysis to allow for non-linear trends. In addition to the effect of time, the main independent variable is treatment groups, a between-subjects factor with 3 levels: STND, TECH and SELF. A priori Helmert contrasts
[38] will be used to test the following comparisons at 3- and 6-months: 1) STND and TECH vs. SELF and 2) TECH vs. STND. We will also examine group by time interactions to test whether change in outcome across time differs by group.

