### Mediation analysis

We hypothesize that the weight loss advantage for those assigned to TECH would be explained (entirely or partially) by TECH’s higher rates of adherence to self-monitoring and attainment of behavioral goals. To test this mediation hypothesis, we will fit a linear mixed model predicting weight loss similar to the model described above, but now including in the regression equation the potential mediating variables corresponding to adherence to self-monitoring. To the extent that adherence mediate the effects of the experimental condition, in the model with adherence included, we expect the coefficient on the treatment group by time interaction variable to be reduced compared to the treatment group by time interaction coefficient from the model without adherence. This difference provides an estimate of the extent to which adherence may mediate the effects of the experimental condition on weight loss. Bootstrapping will be used to estimate the sampling variability of the mediation effect.

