### Sample size and power

We will randomize n=32 participants to each treatment group and assume 6% of participants will drop out by the end of the study so that there will be n=30 participants in each group at the final endpoint. The power calculations below are based on the second Helmert contrast: TECH vs. STND because this contrast contains the fewest number of subjects (30 in each group) and we expect this contrast to have the smallest effect sizes. The first Helmert contrast: STND and TECH vs. SELF has a larger sample size (60 vs. 30) and we anticipate larger effects sizes in this contrast due to the limited intensity of the SELF intervention. Therefore, by powering the study based on the second contrast, we will have more than adequate power for the first contrast.

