#### Weight loss

We measure weight loss at 3, 6, and 12 months. Using data from a previous weight loss trial
[16], we saw standard deviations of 8.4 and 10.7 pounds at months 3 and 6, respectively, with a correlation of 0.86 between the two time points. With 80% power and an n=30 in both groups, we will be able to detect a difference of 6.6 pounds between the two groups.

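### Whole teams of 8 are randomised, but no team effect is named in the model and the stated 80% power rests on 30 versus 30 independent participants

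*Protocol article*

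**What the plan says.** The Protocol article, under Randomization, puts each participant in a team whose members are "assigned to a team with seven other participants, all of whom will be randomized to the same condition", and adds: "Group randomization will be completed by a statistician". Team weight loss competition confirms the team size, since a prize of 400 dollars at 50 dollars per member means 8 members. It also ties members' outcomes together: "The team with the greatest weight loss percentage at each time point will win $400".

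On analysis, Linear mixed modeling says: "The basic modeling approach will entail linear mixed models for longitudinal data". Time (nominal) and treatment group are the only factors named. That section and Study design both call treatment a between-subjects factor. Under Mediation analysis, "Bootstrapping will be used to estimate the sampling variability of the mediation effect", with no resampling unit given.

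Sample size and power bases everything on TECH versus STND because "this contrast contains the fewest number of subjects (30 in each group"). For weight, at 80% power, "we will be able to detect a difference of 6.6 pounds between the two groups". Four further detectable differences follow on the same basis. No ICC, design effect or number of teams appears in any of them.

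**The concern.** The unit of allocation is the team, while the power statements, and the analysis as far as it is described, use the participant. The article also gives reasons to expect team members' outcomes to be correlated. Teams compete for a joint prize meant to make members support each other, STND and TECH teams meet in led group sessions, and TECH teammates see each other's adherence and exchange messages.

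With positive correlation, an analysis that ignores teams gives standard errors that are too small and rejects a true null hypothesis too often. A valid analysis of TECH versus STND compares 4 teams with 4 teams. It therefore has few degrees of freedom and lower power than stated. This contrast carries the main claim for the technology.

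**Working it through.** **Inputs.** Sample size and power: 32 randomised and 30 completing per arm. Randomization: teams of 8. This gives 32/8 = 4 teams per arm, 12 in all, and 30/4 = 7.5 completers per team. SDs and correlations come from the five power subsections. Assumed, because not stated: two-sided alpha of 0.05, and ICC from 0.01 to 0.10.

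**Step 1: reproduce the stated figures with independent participants.** The SD of the month 3 and 6 mean is sqrt((s3² + s6² + 2·r·s3·s6)/4). The detectable difference is (1.960 + 0.842)·SD·sqrt(2/30).

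For weight, SD = sqrt((8.4² + 10.7² + 2·0.86·8.4·10.7)/4) = 9.21 lb, and the detectable difference is 2.802·9.21·sqrt(2/30) = 6.67 lb.

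| Outcome | Computed | Stated | Power at stated value |
|---|---|---|---|
| Weight (lb) | 6.67 | 6.6 | 79% |
| Diet self-monitoring | 0.231 | 0.23 | 80% |
| Activity self-monitoring | 0.223 | 0.22 | 79% |
| Activity (min/week) | 100.1 | 100 | 80% |
| Calories (kcal) | 328 | 375 | 89% |

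The first four match with a design effect of 1, so they contain no allowance for teams. The calorie figure does not follow from its inputs.

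**Step 2: allow for teams.** The design effect is 1 + (7.5 − 1)·ICC, which is 1.065, 1.325 and 1.65 at ICC 0.01, 0.05 and 0.10. The test uses a noncentral t on 12 − 3 = 9 df (all teams) or 8 − 2 = 6 df (the TECH and STND teams only). For weight:

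| ICC | Power for 6.6 lb: normal / 9 df / 6 df | Detectable at 80%: 9 df / 6 df |
|---|---|---|
| 0 | 79 / 70 / 64% | 7.5 / 8.0 lb |
| 0.01 | 77 / 67 / 61% | 7.7 / 8.3 lb |
| 0.05 | 67 / 58 / 52% | 8.6 / 9.2 lb |
| 0.10 | 58 / 49 / 44% | 9.6 / 10.3 lb |

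If cohort is a fixed effect and each team lies in one cohort, one more team-level df goes, leaving 8 or 5. Crediting no variance reduction, the detectable difference is then 7.9 / 8.6 lb at ICC 0.01, 8.8 / 9.6 lb at 0.05 and 9.8 / 10.7 lb at 0.10.

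**Step 3: calories.** On 9 df, 375 kcal has 81% power at ICC 0, 79% at 0.01 and 70% at 0.05. On 6 df it has 76% even at ICC 0.

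**Step 4: type I error if no team term is fitted.** With all 8 members per team, the design effect is 1.07, 1.35 and 1.70. The true two-sided error is 2·(1 − Φ(1.96/sqrt(design effect))), which is 5.8%, 9.2% and 13.3%. Simulation of 4 teams of 8 per arm, analysed by an individual-level t-test, agrees: about 5.6 to 5.9%, 9.1 to 9.4% and 13.3 to 13.5%.

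**The case against.** The strongest reply is that the article gives only a basic modelling approach. It names no random effects at all, and a full analysis plan could add one for team. That stands to this extent: a reader might infer that the analysis will certainly ignore teams, and the article does not establish that. The type I error figures are therefore conditional on the model being fitted as described. The reply does not rescue the power section, because a later team term would lower the power further below the printed 80%.

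Four other readings go further than the text:

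- **The bootstrap resamples individuals.** The resampling unit is not stated, so this is a gap to close and not a demonstrated error.
- **All five detectable differences fail in the same way.** The calorie figure has slack and is roughly met at ICC 0 to 0.01 on 9 df. No ICC is stated there either, so the slack cannot be read as an allowance for clustering.
- **Teams in every arm share a coach and a message board.** The message board belongs to the TECH application. SELF attends one session and gets no coaching calls, and no section says that each team has a single coach. A common ICC across arms is therefore an assumption, and the 9-df figures depend on it.
- **The whole loss of power is due to correlation.** Much of it at low ICC comes from the degrees of freedom: at ICC 0.01 power is 77% by normal approximation but 61 to 67% on 6 to 9 df. Using team-level degrees of freedom is conservative but defensible with 4 teams per arm.

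**Conclusion.** The point holds for the power section as written, and conditionally for the analysis. Allocation is by team, yet four of the five detectable differences are independent-participant calculations, so the stated 80% power is not delivered for any positive ICC. Over the assumed ICC range, the weight difference detectable at 80% power is 7.7 to 9.6 lb on 9 df or 8.3 to 10.3 lb on 6 df, against 6.6 lb stated. If the model has no team term, the nominal 5% test of TECH versus STND runs at about 6%, 9% and 13% at ICC 0.01, 0.05 and 0.10.

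The sizes rest on the assumed ICC, an ICC common to the arms compared, two-sided alpha of 0.05, and 7.5 completers per team (8 for the type I error). The direction does not depend on which positive ICC is chosen. Because the main contrast is affected, this should be corrected before analysis.

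**What to change.** - **Linear mixed modeling:** add a random effect for team within arm, keep it even if its estimated variance is zero, and use small-sample degrees of freedom (Kenward-Roger, or a team-level test). Do not add baseline as a covariate across the board as part of this change: Study design makes baseline one of the four levels of the time factor, so it may already be a response.
- **Mediation analysis:** state that the bootstrap resamples whole teams within arm, or use a team-level permutation.
- **Sample size and power:** restate the detectable differences over a declared ICC range, with degrees of freedom that match the final model. For weight at ICC 0.01 to 0.10, without a cohort term, that is 7.7 to 9.6 lb (9 df) or 8.3 to 10.3 lb (6 df). With cohort as a fixed effect and no variance reduction credited, it is 7.9 to 9.8 lb (8 df) or 8.6 to 10.7 lb (5 df). Recompute the calorie figure from its own inputs first.

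The cost is less favourable stated figures and wider intervals. The team competition already requires team membership to be known, and no more participants are needed.
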